**Research Design.** This study will randomize at least 120 overweight and obese male and female Veterans with BED or subclinical BED to one of two arms (ROC or CBT). The study data manager, who will have no contact with research participants, will conduct randomizations and monitor allocations throughout the study to alert the PI of any systematic differences in additional demographics (age, race/ethnicity) that may arise.

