## Treatment Arms

Both interventions arms will be matched on contact frequency and time. All treatment groups will include up to 20 participants, will be 60 minutes in length and will meet weekly for 4 months, and twice monthly for the 5th month

Table 1. Differences between ROC and CBT

|                                       | ROC                                                                                                                                                                                                                                                                          | CBT                                                                                   |
|---------------------------------------|------------------------------------------------------------------------------------------------------------------------------------------------------------------------------------------------------------------------------------------------------------------------------|---------------------------------------------------------------------------------------|
| Dietary prescription           | Sessions focus on learning to control physiological and psychological responding to food, and to eat less of foods that are palatable when physically sated. Participants will learn general food intake literacy, to pick nutritious foods, and physiological energy needs. | None
Participants are encouraged to incorporate a variety of foods into their diet |
| Self-monitoring                | Hunger, craving and food intake                                                                                                                                                                                                                                              | Antecedents, behaviors, consequences and thoughts surrounding binge episodes          |
| Experiential learning          | Participants bring meals and/or palatable foods to each session. Hunger and satiety is monitored in session during meals. Exposures to highly craved foods are conducted in session.                                                                                         | None                                                                                  |

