| Physical activity prescription | Physical activity is used to help regulate physiological and psychological responding to food cues.                                                                                                                                                                          | None                                                                                  |
| Goal setting                   | Goal setting focuses on self-monitoring and practicing mastery and toleration of physiological /psychological arousal, as well as food intake and physical activity                                                                                                          | Goal setting focuses on self-monitoring of food intake, thoughts and behaviors.       |
| Coping skills                  | Methods for managing psychological and physiological arousal. Discussed each week in regards to mastery and toleration of physiological /psychological arousal.                                                                                                              | Cognitive restructuring, stress management, behavior chains to reduce binge eating    |

(total treatment duration = 5 months, 18 meetings). Descriptions of the treatment arms follow and key differences between the treatment arms are outlined in Table 1. All treatment sessions will be audiorecorded for supervision and fidelity purposes.

**Regulation of Cues (ROC).** The ROC program provides psychoeducation, coping skills, self-monitoring and experiential learning. Physical activity will be promoted to improve self-regulatory strength and to help participants master and tolerate physiological and psychological arousal, resist cravings and overeating.

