**Psychoeducation.** The ROC program provides psychoeducation at each group visit by describing a “Deceptive Hunger”, which is a way that the environment “tricks” the body into overeating past nutritional needs. The overall goal of psychoeducation is to increase participant’s awareness of the reasons why they may overeat, and to relieve participants from guilt regarding overeating by helping them understanding the processes by which these phenomena occur. Both lack of sensitivity to appetite and satiety cues and increased sensitivity to food cues will be discussed. Physiological, neurobiological and environmental models of overeating past nutritional needs are presented in lay language so that participants can understand their vulnerabilities to overeating. The concepts are taught using a chronic disease model in which the individual is considered to have the biological vulnerability to overeat that is amplified by the current obesogenic food environment. Participants are provided information about basic learning theory and how physiological responses to food cues develop and can be managed.

**Coping skills.** Coping skills will be taught to accompany each Deceptive Hunger. Coping skills are presented to assist in mastery and toleration of food cue sensitivity. Coping skills include physiological skills (deep breathing, relaxation, and mindfulness), behavioral skills (delay, activity substitution) and cognitive skills (cognitive restructuring, distraction).

**Experiential learning and self-monitoring.** In each session, participants will complete an experiential learning exercise. During visits 1-8, participants will be taught about hunger and satiety dysregulation. Participants will be taught to monitor their hunger in a self-monitoring booklet on a 1-5 scale, with 1 “starving” and 5= “stuffed”. Participants will be instructed to self-monitor hunger and satiety before, during and after each meal, as well as 10 and 20 minutes after eating for a minimum of two meals/snacks per day. Participants will bring dinner and all groups will start by eating dinner and monitoring their hunger with prompting from the group leader.

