The initial focus in CBT is on eliminating binge eating patterns by establishing regular, healthy eating patterns. Participants are taught to self-monitor their food intake and eating patterns, binge episodes, thoughts, and mood pre- and post- binge, as well as the circumstances and environment surrounding eating. Examination of the monitoring records are the primary focus of the group treatment. Participants are taught to identify problems in eating, thinking, and mood patterns that served to trigger binge episodes through self-monitoring and to gradually develop alternative patterns aimed at facilitating healthy, binge-free eating patterns. Participants are taught to eat a healthy variety of foods, and later on in treatment, they are taught to integrate the binge foods into their usual meals. CBT treatment consists of three phases.

In the first phase, focus is on reducing binge eating by normalizing eating patterns to reduce dietary restraint and incorporating a variety of foods into the diet. In the second phase, focus is on addressing problematic cognitions related to eating shape and weight. Further, emphasis is placed on identifying alternative responses to stress than binge eating. Finally, in the third phase, participants are instructed to anticipate high-risk situations in which a lapse might occur and to outline a plan to prevent such a lapse as well as develop long-term realistic expectations for their eating habits.

***Quality control, fidelity and supervision of intervention.*** The intervention for this study will be provided by licensed clinical psychologists and postdoctoral fellows. All interventionists in ROC will attend a 2-day training with [name] and [name] and all interventionists in CBT will attend a 2-day training with [name] and [name]. Intervention sessions will be audiotaped for ongoing performance monitoring. Random samples (e.g. 30% or more) of all intervention sessions will be rated for fidelity by an independent rater using a measure created for this study.

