**Primary Aim 2:** Efficacy of ROC and CBT on changes in binge eating (*as measured by the EDE; EDE-Q and BES*), at mid-treatment, post-treatment and 6-months post-treatment timepoints. LME models with dummy-coded indicators for planned treatment comparisons between ROC and CBT, and a continuous term for time selected after evaluating non-linearity. Between-group (ROC vs. CBT) differences in change in binge eating (Primary Aim 2) will be estimated in models with planned covariates (age, gender), baseline BMI, and corresponding baseline values for each outcome. The GLME for counts of binge episodes and LME model for continuous symptom inventories provide maximum likelihood parameter estimates based on all of the available data, allowing for the inclusion of cases with missing data and the modeling of the covariance error structure of the data across the assessment points. Interactions of between-group indicator and time will assess whether differences in binge eating dissipate from active treatment compared to the 6-month follow-up timepoint.

**Primary Aim 3:** Efficacy of ROC and CBT on changes in weight loss (BMI) and energy intake (kcal/day), at mid-treatment, post-treatment and 6-months post-treatment time points will be evaluated with (G)LME models. Between-group (ROC vs. CBT) differences in change in BMI and energy intake will be estimated in models with planned covariates (age, gender), and corresponding baseline values for each outcome.

**Secondary Aim 1:** Efficacy of ROC and CBT on changes in food responsivity (FR scale; psychophysiological responding to food, reward-based eating) and satiety responsiveness (SR scale, WLT), using GLME adjusted for corresponding baseline values and planned covariates mirroring primary analyses. We also will use (G)LME to assess between-group differences in measures of reactivity to food cues using psychophysiological measures of EMG (salivation), heart rate and HRV at each follow-up.

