### **15. RISK MANAGEMENT PROCEDURES AND ADEQUACY OF RESOURCES**

*There is a degree of inconvenience for Veterans who may miss work, activities, meetings, etc. to participate in the study.* It is possible that missed work could result in decreased income. At CHEAR, assessments are conducted in the morning, afternoon, evening and on Saturdays if necessary to reduce the impact of assessments on Veteran's work or activities. Participants will be made aware of the weekly treatment night during the screening process. If a Veteran is busy with activities or other commitments on that evening, they will be offered to wait for another cohort which will be offered on an alternative evening.

*There is a risk of reactivity to assessment procedures.* For some participants, disclosing information about mental health symptoms and eating behaviors may be uncomfortable. Questions regarding individual behaviors, emotions or attitudes may be considered sensitive to some participants. This risk will be mitigated by having well supervised assessors conduct the assessments, thereby being aware of emotional reactivity or stress response in an early form. Veterans will be notified that they may decline to answer any questions due to discomfort or may choose to end their participation in screening if no longer interested.

*Risk management for psychiatric concerns identified in assessment*

For any unidentified/unreported psychiatric concerns identified during assessments for this project, we will execute the following protocol:

- The Veteran will be notified of concerns identified.
- The Veteran will be given a list of referrals in the community or referred back to the VASDHS mental health team (depending on source of recruitment). [name] and [name] are both licensed clinical psychologists, and experienced in assessing psychiatric risk. CHEAR has an extensive list of community mental health referrals, some which offer treatment at no or low-cost.

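### Both arms are delivered in therapy groups of up to 20, but no between-arm model in the Analyses Plan has a term for therapy group; if outcomes correlate within groups, the ROC–CBT standard errors are too small

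*Protocol*

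**What the plan says.** Treatment Arms sets the delivery format for both interventions: "All treatment groups will include up to 20 participants", with contact matched between arms ("total treatment duration = 5 months, 18 meetings"). The group is the working unit in each arm. In ROC, "all groups will start by eating dinner and monitoring their hunger with prompting from the group leader". In CBT, "Examination of the monitoring records are the primary focus of the group treatment". Section 15 shows that groups run in successive cohorts: a participant who cannot attend the treatment evening is told that "they will be offered to wait for another cohort" is an option. On size, the Research Design paragraph says: "This study will randomize at least 120 overweight and obese male and female Veterans".

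The Analyses Plan names its models and covariates:

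- **Primary Aim 1:** logistic regression for treatment completion, Cox regression for time to dropout, a generalized linear model for sessions attended and a linear model for acceptability. All are adjusted for the planned covariates and baseline BMI.
- **Primary Aim 2:** linear and generalized linear mixed models adjusted for age, gender, baseline BMI and the baseline outcome. The dependence mentioned is "the modeling of the covariance error structure of the data across the assessment points".
- **Primary Aim 3:** mixed models adjusted for age, gender and the baseline outcome.
- **Secondary Aim 1:** mixed models that follow the primary analyses.

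Wherever the Analyses Plan speaks of groups, it means the arms. Therapy group, cohort and leader enter no model.

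**The concern.** People who spend 18 sessions together under the same leader may end up more alike than people in different groups. Because a therapy group delivers only one treatment, variation between groups goes directly into the ROC–CBT contrast. A covariance structure for repeated measures within a person does not capture it: two members of one group are still treated as independent.

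Aim 1 is exposed in the same way. Attendance and dropout can share a group or leader influence, and under Maximizing Retention it is the group leader who telephones participants who miss a visit. The Aim 1 models carry no dependence term at all.

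At stake are the confidence intervals and tests for all three primary aims and Secondary Aim 1. With positive within-group correlation the intervals are too narrow, and a difference between arms is declared too often when there is none.

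**Working it through.** **No stated figure to reproduce.** The protocol gives a sample size but no significance level, power, effect size, SD, ICC or dropout rate for the efficacy comparisons.

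**Inputs from the protocol.** At least 120 randomized; two arms; groups of at most 20.

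**Assumptions.** 1:1 allocation (60 per arm), because no ratio is stated. Two-sided 5% test, because the only level given is 95% for the bootstrap intervals of indirect effects. ICC from 0.01 to 0.10. Group size m of 20 (60/20 = 3 groups per arm, the fewest possible for 60) or 10 (6 per arm), because only the maximum is stated.

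**Formulas.** Design effect DE = 1 + (m − 1) × ICC. True error of an unadjusted nominal 5% test = 2 × [1 − Φ(1.96/√DE)].

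Example, m = 20, ICC = 0.05: DE = 1 + 19 × 0.05 = 1.95; 1.96/√1.95 = 1.40; error = 16.1%.

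| ICC | DE, m = 20 | Type I error, m = 20 | DE, m = 10 | Type I error, m = 10 |
|---|---|---|---|---|
| 0 | 1.00 | 5.0% | 1.00 | 5.0% |
| 0.01 | 1.19 | 7.2% | 1.09 | 6.1% |
| 0.02 | 1.38 | 9.5% | 1.18 | 7.1% |
| 0.05 | 1.95 | 16.1% | 1.45 | 10.4% |
| 0.10 | 2.90 | 25.0% | 1.90 | 15.5% |

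At ICC 0.05 the unadjusted standard error is 1/√DE = 0.72 of the true one with groups of 20, and 0.83 with groups of 10. Effective N is 120/1.95 ≈ 62 and 120/1.45 ≈ 83.

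**Simulation check** (40,000 trials per setting, 60 per arm, single outcome). The unadjusted t test rejected in 7.4%, 9.7%, 16.2% and 25.6% of null trials with groups of 20, and in 6.1%, 7.3%, 10.4% and 15.7% with groups of 10, at ICC 0.01, 0.02, 0.05 and 0.10. A t test on group means rejected in 4.8% to 5.1%.

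**Cost in precision, ICC 0.05.** Under independence the detectable difference at 80% power is (1.96 + 0.84) × √(2/60) ≈ 0.51 SD. Respecting groups, it is approximately (t₀.₉₇₅ + t₀.₈₀) × √(2 × DE/60) on between-group degrees of freedom:

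- 12 groups of 10, 10 df: (2.228 + 0.879) × √(2 × 1.45/60) = 3.107 × 0.220 ≈ 0.68 SD.
- 6 groups of 20, 4 df: (2.776 + 0.941) × √(2 × 1.95/60) = 3.717 × 0.255 ≈ 0.95 SD.

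**Effect of adding a fixed cohort term.** With one group per arm per cohort (assumed), 6 groups form 3 cohorts and 12 groups form 6. The degrees of freedom fall to 2 and 5, and the same formula at the same DE gives about 1.37 SD and 0.77 SD.

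**The case against.** The strongest reply is that this argues from silence. The statistical analysis plan is not available, the protocol does not list its random effects, and its sentence on covariance describes what mixed models permit without excluding other terms. A group intercept could be added without contradicting it. This is fair as far as it goes, but it does not remove the point. The protocol goes beyond naming a model class: it lists covariates and names one dependence structure, and it gives Aim 1 ordinary single-level models. An analysis that followed that text would omit the group level; one that included it would be adding to the text.

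Several stronger readings are tempting, and the documents do not support them:

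- **That the 5% error rate is known to be missed.** No level is stated for the efficacy tests, and inflation needs a positive ICC, for which no value is given. At 0.01 it is modest. The relevant ICC is the residual one after adjustment for baseline values over repeated follow-ups, whereas the calculation above is for one unadjusted time point.
- **That there are only three groups per arm.** Twenty is a maximum and 120 a minimum, so three is the smallest possible number under 1:1 allocation.
- **That both arms share meals and exposures.** These belong to ROC; Table 1 lists no experiential learning for CBT. The case for CBT rests on its group work and leader.
- **That groups are closed, or that membership is already recorded.** Neither is stated.
- **That the treatment estimate is biased.** Random group effects add variance to the contrast; they do not shift it systematically.

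**Conclusion.** The point holds in conditional form. Both arms are group treatments nested in arm, and the analysis as written has no group level, so any positive within-group correlation makes the ROC–CBT standard errors too small. The direction does not depend on the assumptions; the size does. With 60 per arm, a two-sided 5% test and ICC between 0.01 and 0.10, true type I error runs from about 7% to 25% with groups of 20, the least favourable size allowed, and from about 6% to 16% with groups of 10. The protocol offers no reason to take the ICC as zero, and its reliance on group process makes zero hard to defend. The Analyses Plan should be amended before the data are analysed.

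**What to change.** Amend the Analyses Plan as follows.

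- **Aims 2 and 3, Secondary Aim 1 and the linear acceptability model:** include a random intercept for therapy group. In the linear models, fit by REML and test the arm effect with Kenward–Roger or Satterthwaite degrees of freedom.
- **Logistic, count and Cox analyses:** those corrections do not carry over routinely. Use a group random effect or shared frailty, or a group-level summary analysis with between-group degrees of freedom. A variance from as few as six groups is poorly estimated, so choose the method in advance. Cluster-robust errors without a small-sample correction are inadequate with so few groups.
- **Cohort:** do not require a fixed cohort effect; with few cohorts it uses up most of the between-group degrees of freedom.
- **Data and reporting:** confirm that group and leader identifiers are held for every participant, and report the ICC for each primary outcome.

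If the identifiers exist, the change is one of analysis wording only; no visit, procedure or treatment is altered. The cost is wider confidence intervals. For a true difference of 0.51 SD, which would have 80% power under independence, power at ICC 0.05 on between-group degrees of freedom is about 56% with 12 groups of 10 and 34% with 6 groups of 20. Even at ICC 0, a group-level test would have 71% and 56%, purely from the loss of degrees of freedom.

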**6. SPECIFIC AIMS**

**Primary Aim 1:** Evaluate the feasibility and acceptability of ROC and CBT.

**Primary Aim 2:** Compare the efficacy of ROC and CBT on binge eating over the duration of the study.

**Primary Aim 3:** Compare the efficacy of ROC and CBT on weight loss (BMI) and energy intake (as measured by 24-hour dietary recalls) over the duration of the study.

**Secondary Aim 1:** Determine the extent to which ROC and CBT influence underlying mechanisms of action, including responsivity to food cues, satiety responsiveness, and reward-based eating.

**Exploratory Aim 1:** To evaluate moderators of treatment (age, gender, binge eating status, satiety responsiveness, responsivity to food cues, reward-based eating) and mediators of treatment outcomes (responsivity to food cues, satiety responsiveness, reward-based eating, physical activity).

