#### ***Orientation Visit:***

At this visit, UCSD study staff will again describe the study, the two treatment arms, randomization methods, expectations for participation, and incentives for time and effort to ensure participants completely understand what they are signing up for and be presented with the informed consent. Participants who agree to participate and complete the consent form will have their height and weight measured and schedule their baseline assessment visit.

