*Psychophysiological responding to food (baseline, post-treatment and 6-months post-treatment)* is a measure of physical responses to highly craved foods. Electrophysiological recordings will all be sampled at 250 Hz. Participants complete three measurement phases in this task; baseline, food exposure, and recovery. During the baseline measurement phase and the recovery phase, participants will sit quietly for 6 minutes in a quiet private room. During the food exposure measurement phase, their highly craved food (identified by the participant) will be placed on the table in front of them. The participant is prompted to hold and smell the food and think about eating it for 6 minutes. Once the food exposure measurement phase is completed, the food is taken away and the participant completes the recovery phase (sit quietly for 6-minutes). Heart rate and Heart Rate Variability (HRV) will be measured using two Ag±AgCl electrodes, one attached on the left side of the subject, the other attached under the right collarbone. R-waves will be detected off-line with a template matching procedure, and inter-beat intervals will be calculated. Heart rate and HRV will be measured continuously during the food exposure tasks.

**Reward-Based Eating** (all assessment time points and monthly during treatment). The Reward-Based Eating Drive scale (RED-13) was adapted from the RED-9 to evaluate a broader spectrum of reward-related eating. The RED-13 has demonstrated strong reliability and validity.

**24-hour Dietary Recalls** (baseline, post-treatment and 6-month follow-up assessment time points). Dietary intake will be assessed with 3 24-hour dietary recalls on 3 non-consecutive days, via telephone interview outside of the assessment visit; two during the week and one on a weekend day. All interviews will use the Nutrition Data Systems for Research (NDS-R) nutrient calculation software. The multiple-pass interview technique will be used to prompt for complete food recall and descriptions and the Posner 2-dimensional food portion visual aid will be used to assist in portion size estimation. All dietary interviews will be administered by trained assessment staff from the UCSD Nutrition Shared Resource, blinded to study group assignment.

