## **Analyses Plan**

**Primary Aim 1:** Feasibility will be evaluated through the assessment of attendance and retention rates of individuals in the ROC and CBT treatments for treatment completers, dropouts and number of sessions attended. Logistic regression models will be used with planned covariates and baseline BMI to estimate between-group difference in odds of treatment completion, defined by receiving a sufficient dose of treatment (i.e. >70% of sessions). Cox proportional hazards models adjusted with planned covariates and baseline BMI to evaluate differences between groups in time to dropout defined as missing four consecutive treatment sessions. Descriptive data will be calculated and between-group differences in counts of sessions attended will be compared between groups using a generalized linear model to accommodate expected non-normal distributions and will include planned covariates and baseline BMI in the model. Model selection will proceed by testing assumptions and improvements in fit afforded by candidate models that could account for over-dispersion or a large number of participants with no-missed sessions (e.g. Poisson vs. negative binomial or zero-inflated counts). To assess acceptability, we will use linear models adjusted with planned covariates and baseline BMI to estimate between-group differences on the acceptability questionnaire, a continuous measure of both satisfaction and liking of the treatment they received.

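### The Primary Aim 3 energy-intake model leaves out baseline BMI, which the Aim 1 and Aim 2 models include: a small consistency and efficiency point

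*Protocol*

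**What the plan says.** The protocol's Analyses Plan (section 9) names the covariates aim by aim.

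- **Primary Aim 1.** The logistic, Cox, count and linear models all take the planned covariates plus baseline BMI. For treatment completion: "Logistic regression models will be used with planned covariates and baseline BMI to estimate between-group difference in odds of treatment completion". For acceptability: "linear models adjusted with planned covariates and baseline BMI".
- **Primary Aim 2 (binge eating).** Between-group differences "will be estimated in models with planned covariates (age, gender), baseline BMI, and corresponding baseline values for each outcome".
- **Primary Aim 3 (BMI and energy intake in kcal/day).** Between-group differences "will be estimated in models with planned covariates (age, gender), and corresponding baseline values for each outcome". Baseline BMI is not listed as a separate term.

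Section 6 makes energy intake an outcome of Primary Aim 3. Baseline BMI needs no new measurement. Under Orientation Visit, "Participants who agree to participate and complete the consent form will have their height and weight measured and schedule their baseline assessment visit", and the Measures section lists anthropometry again at baseline. On the outcome itself, Measures says: "Dietary intake will be assessed with 3 24-hour dietary recalls on 3 non-consecutive days, via telephone interview outside of the assessment visit". Recalls are taken at baseline, post-treatment and 6-month follow-up.

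**The concern.** The Aim 3 sentence serves two outcomes at once. For BMI, the baseline value of the outcome is baseline BMI, so a separate term would be redundant. For energy intake, the same wording drops a covariate that the sponsor uses in every Aim 1 and Aim 2 model. This looks like a by-product of sharing one sentence, because no reason for treating energy intake differently is stated.

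Two small things are at stake. First, if baseline BMI predicts follow-up intake beyond what baseline intake, age and gender already explain, some explainable variance stays in the error term. Baseline intake is an average of three recalls, so it need not capture everything that BMI could add. Second, the primary aims carry two covariate sets. Secondary Aim 1 says its covariates follow the primary analyses, and a reader cannot tell which set is meant.

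**Working it through.** **Side by side**

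| Model | Age, gender | Baseline of outcome | Baseline BMI |
|---|---|---|---|
| Aim 1 models | yes | not applicable | yes |
| Aim 2, binge eating | yes | yes | yes |
| Aim 3, BMI | yes | yes | yes (it is the baseline of the outcome) |
| Aim 3, energy intake | yes | yes | **no** |

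The text confirms the omission, for energy intake only.

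**Size.** The protocol gives no power figure, standard deviation or correlation for energy intake, so there is no stated figure to reproduce. What follows rests on assumptions, shown as ranges.

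Inputs:
- N = 120 randomized (Research Design). Equal arms of 60 are assumed, since no ratio is stated.
- One follow-up time point, analysed by ANCOVA, as a simplification of the planned mixed model.
- r = partial correlation of baseline BMI with follow-up intake, given arm, age, gender and baseline intake. Assumed.
- Two-sided 5% level, with the effect set to give 80% power without BMI: (1.960 + 0.842) × √(4/120) = 0.51 residual SD. Assumed.

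Formula: adding BMI multiplies the variance of the treatment estimate by (1 − r²) × df/(df − 1). Here df = 120 − 6 = 114 residual degrees of freedom with BMI in the model (intercept, arm, age, gender, baseline intake, BMI). The cost factor is 114/113 = 1.0088.

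| r | (1 − r²) × 1.0088 | Change in SE | Equivalent participants | Power |
|---|---|---|---|---|
| 0 | 1.0088 | +0.4% | −1 | 79.7% |
| 0.1 | 0.9988 | −0.1% | 0 | 80.0% |
| 0.2 | 0.9685 | −1.6% | +4 | 81.2% |
| 0.3 | 0.9181 | −4.2% | +11 | 83.2% |

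Break-even is where 1 − r² = 113/114, so r² = 1/114 = 0.0088 and r ≈ 0.09. Below that, the extra term costs slightly more than it returns. With 90 participants analysed instead (an assumption), the range from r = 0 to r = 0.3 is +0.6% to −4.0%.

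**Which r is reasonable?** Let m be the BMI–intake correlation (assumed equal at both times) and b the correlation of intake with itself over time. Ignoring age and gender,

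r = m(1 − b) / √[(1 − b²)(1 − m²)].

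- m = 0.1, b = 0.7: r = 0.04, or 0.2% of residual variance.
- m = 0.2, b = 0.5: r = 0.12, or 1.4%.
- m = 0.3, b = 0.5: r = 0.18, or 3.3%.
- m = 0.4, b = 0.3: r = 0.32, or 10.3%.

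Most of the assumed grid lies at or below r = 0.25. The last case is the most favourable corner. These percentages are before the cost of the degree of freedom.

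**The case against.** The strongest reply is that nothing here is wrong. The protocol pre-specifies a baseline-adjusted model for energy intake, with age and gender. It defines the planned covariates as age and gender, lists baseline BMI separately, and nowhere commits to BMI in every model. Different outcomes may have different covariate sets, and one further prognostic term could be settled in the analysis plan. All of this stands, except that the protocol does not leave the matter open: it writes out the covariate list for this model, and the list differs from its neighbours.

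The gain may also be nil. The conversion above ignores age and gender, which may already carry part of any BMI signal, and entry at BMI 25 or above restricts the range, which tends to weaken correlations. That also stands and points to the lower half of the range.

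Three stronger readings are tempting, and the documents support none of them.

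- **That the omission biases the comparison.** Under randomization it does not. Chance imbalance in BMI is already reflected in the standard error, and adjusting for baseline intake removes part of it.
- **That adding BMI is a free gain.** It costs one degree of freedom, and below r of about 0.09 the net effect is a slight loss.
- **That intake is driven by body size.** The protocol does not say so. The outcome is intake recalled by telephone, and its relation to BMI given baseline intake is not stated.

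**Conclusion.** The point holds as a minor one. As written, the energy-intake model omits baseline BMI, the Aim 1 and Aim 2 models include it, and no reason is given. The planned comparison is valid, and no conclusion of the trial depends on the change.

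Over assumed partial correlations of 0 to 0.3 with 120 participants, adding BMI moves the standard error by between +0.4% and −4.2%, and power from 80% to between 79.7% and 83.2%. This rests on equal arms, one follow-up time point, no missing recalls and a partial correlation the documents do not supply. The change is still worth making: the worst case is small, the plausible gain is up to a few percent of the standard error, and it leaves one covariate rule across the primary aims.

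**What to change.** In the Analyses Plan, Primary Aim 3, add after the covariate sentence: *energy-intake models additionally adjust for baseline BMI, as in Aims 1 and 2.* If the omission is deliberate, state the reason instead. Make the change before outcome data by arm are examined.

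The cost is one clause and one degree of freedom, at most about 0.4% on the standard error with 120 participants. No new data are needed, and the BMI model is unaffected.
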